## Abstract

**Background:**

Concerted effort to control malaria has had a substantial impact on the transmission of the disease in the past two decades. In areas where reduced malaria transmission is being sustained through insecticide-based vector control interventions, primarily long-lasting insecticidal nets (LLINs) and indoor residual spraying (IRS), non-insecticidal complementary tools will likely be needed to push towards malaria elimination. Once interruption in local disease transmission is achieved, insecticide-based measures can be scaled down gradually and eventually phased out, saving on costs of sustaining control programs and mitigating any unintended negative health and environmental impacts posed by insecticides. These non-insecticidal methods could eventually replace insecticidal methods of vector control.

House screening, a non-insecticidal method, has a long history in malaria control, but is still not widely adopted in sub-Saharan Africa. This study aims to add to the evidence base for this intervention in low transmission settings by assessing the efficacy, impact, and feasibility of house screening in areas where LLINs are conventionally used for malaria control.

**Methods:**

A two-armed, household randomized clinical trial will be conducted in Mozambique, Zambia, and Zimbabwe to evaluate whether combined the use of house screens and LLINs affords better protection against clinical malaria in children between 6 months and 13 years compared to the sole use of LLINs. Eight hundred households will be enrolled in each study area, where 400 households will be randomly assigned the intervention, house screening, and LLINs while the control households will be provided with LLINs only. Clinical malaria incidence will be estimated by actively following up one child from each household for 6 months over the malaria transmission season. Cross-sectional parasite prevalence will be estimated by testing all participating children for malaria parasites at the beginning and end of each transmission season using rapid diagnostic tests.

CDC light traps and pyrethrum spray catches (PSC) will be used to sample adult mosquitoes and evaluate the impact of house screening on indoor mosquito density, species distribution, and sporozoite rates.

**Discussion:**

This study will contribute epidemiological data on the impact of house screening on malaria transmission and assess the feasibility of its implementation on a programmatic scale.

**Trial registration:**

ClinicalTrials.gov PACTR202008524310568. Registered on August 11, 2020.

**Supplementary Information:**

The online version contains supplementary material available at 10.1186/s13063-021-05768-7.

## Administrative information

Note: the numbers in curly brackets in this protocol refer to SPIRIT checklist item numbers. The order of the items has been modified to group similar items (see http://www.equator-network.org/reporting-guidelines/spirit-2727-statement-defining-standard-protocol-items-for-clinical-trials/). above the administrative information table.

## Introduction

### Background and rationale {6a}

Insecticide-based malaria control tools have led to significant reductions in malaria transmission, morbidity, and mortality in the past two decades [1]. However, recent reports indicate that progress in malaria control has stalled [2, 3] mainly due to the reallocation of funds previously available for malaria control, lack of political commitment to invest in malaria control programs and defined limits of current vector control strategies. That lack of adequate funding has resulted in the weakening of malaria control programs and the attendant coverage gaps of malaria interventions. One of the pillars of the Global Technical Strategy (GTS) [4] to reduce malaria morbidity and mortality by 90% globally is to ensure universal access to malaria prevention interventions [4] at an annually recurrent cost of between $6.4 and $8.7 billion from 2020 to 2030 [4]. In 2018, only $2.7 billion was invested in malaria control, about one third of the amount needed to attain the 2020 GTS targets [3]. Given the current COVID-19 pandemic [5] and its dire economic consequences worldwide, it is unlikely for this funding gap to be met any time soon. Consequently, the GTS goal of 90% coverage with currently supported malaria interventions will fall short, leaving a significant proportion of the at-risk population unprotected. This coverage gap may lead to a resurgence of malaria in regions where it had been previously been controlled and might jeopardize the elimination goal, especially in countries at the fringe of malaria transmission, like the Southern African Region [6]. Mathematical models estimate significant funding is needed to achieve the GTS strategy [4]. However, the return of investment of elimination (up to $300 billion) far outweighs the input costs, not to mention other costs saved from reduced malaria treatment and increase in the labor force from reduced illness [7]. Given the status of the world economy, it is unlikely that these funds will be available [8]. It is therefore prudent that financing mechanisms for malaria control are reviewed, adjusted, and diversified to fit the endemic countries that rely on international funding [9] and sustainable novel strategies for malaria control are developed for these settings [10].

In 2001, leaders from African Union countries pledged to commit 15% of their national budget to improve the health of their countries [11]. Two decades later, these commitments are yet to be honored [12]. This lack of political will by African governments, where the malaria burden is highest, further widens the coverage gap of malaria interventions and escalates the threat to progress made in malaria control. Consequently, new strategies are being developed to keep malaria control and elimination high on the developmental and political agenda and sustain financing of control programs to achieve the 2030 GTS targets [13]. These strategies include developing multisectoral partnerships with sectors such as housing and agriculture to tackle malaria transmission, regional initiatives such as the Eliminate-8 (E-8) initiative for cross-border surveillance of malaria, expanding the domestic financing base and strengthening the health systems of endemic countries [4]. In 2018, the WHO launched the High burden High Impact initiative (HBHI) which advocated for the development of country tailored goals and strategies towards malaria control and elimination. This initiative also emphasized the translation of stated political commitments into resources and tangible actions [9].

Malaria transmission is inter-linked with socio-demographic and environmental factors [7]. Socio-economic development is likely to improve housing, nutrition, access to health care, and education which all result in improved health and reduce malaria transmission. Environmental factors such as climate change and land use will likely change the geographic distribution of malaria and shift malaria transmission upwards or downwards. Population growth and movement into urban areas is will reduce malaria transmission because of improved standards of living, access to health care, and destruction of mosquito breeding sites [7]. All these factors, coined, megatrends [14], will lead to reduced malaria transmission overall, yet are unlikely to lead to elimination unless the tracks are laid down now to diversify interventions and to take advantage of some of the changes [7].

The WHO and the international malaria community have recommended the implementation of integrated vector management (IVM) strategy to sustainably control, and ultimately, eliminate malaria [15] and especially emphasized the need for local action [9]. IVM underscores the need for multi-sectoral collaboration and action, evidence-based decision-making, social mobilization, and utilization of existing systems and locally available resources [16].

Most malaria transmission in sub-Saharan Africa still occurs indoors despite increased vector control efforts with intra-domiciliary measures, LLINs, and IRS [17], with reports estimating human exposure to mosquito bites to be greater indoors than outdoors [18–20]. This occurrence highlights the need for the development of tools that can attack this exposure to mosquitoes indoors despite the extensive employment of LLINs and IRS.

Historically, house screening studies have demonstrated a reduction in mosquito numbers indoors and subsequently reduced the risk of malaria transmission [21, 22]. However, these studies did not generate robust evidence for house screening [22]. House screening works by physically deterring the entry of mosquitoes into houses, thereby reducing human exposure to infectious bites indoors [23, 24]. In addition, the use of non-insecticidal house screens presents an opportunity for minimizing reliance on insecticide-based measures for malaria control. This strategy could supplement the primary insecticide-based tools in settings where there is an extensive spread of insecticide resistance as it would target all vectors, thereby having a greater impact on malaria transmission than the sole use of insecticide-based measures which only targets susceptible mosquitoes. Gradually, as malaria gets controlled and eliminated this might become a dominant tool to maintain the success.

Despite its potential, house screening is yet to be embedded into the malaria control policy as a vector control tool. This is because with the advent of DDT in the 1950s, malaria control shifted focus to insecticide-based interventions and as a result, limited evidence on the epidemiological impact of environmental management, including house screening, was generated [22].

To date, only two randomized controlled trials have been conducted to evaluate the impact of house screening against malaria transmission [25, 26]. Another house screening trial is currently being implemented in the Gambia [27]. However, there is a need for extensive data from different eco-epidemiological settings in order to incorporate house improvement into an integrated program for malaria control. Consequently, the World Health Organization-Regional Office for Africa (WHO-AFRO) and the International Centre of Insect Physiology and Ecology (*icipe*) are conducting a multi-country study in southern Africa on the additional impact of house screening on malaria transmission and clinical disease outcomes to support the formulation of policy guidelines around house improvement for malaria control. This study is being implemented by the Ministries of Health in Mozambique, Zambia, and Zimbabwe, through their respective National Malaria Control Programmes (NMCP) with technical assistance from WHO-AFRO and *icipe*.

House screening presents a pragmatic tool for malaria control as housing conditions are improving in sub-Saharan Africa, and malaria control programs can tap into this opportunity to develop housing that protects against malaria transmission [22]. In addition, improved housing might offer an avenue for sustainable malaria control as it will be cheaper compared to LLINs and IRS and may replace these insecticide-based measures in the long run.

### Objectives {7}

The overall aim of the study is to assess the efficacy, impact, and feasibility of house screening as an additional anti-malaria intervention in areas where LLINs are conventionally used for malaria control in Zambia, Zimbabwe, and Mozambique.

#### Clinical outcomes

##### Primary objective

To evaluate whether house screening of all mosquito entry points (in semi-modern houses) in addition to LLIN use provides greater protection against clinical malaria in children between 6 months and 13 years than the sole use of LLINs.

##### Secondary objective

To evaluate the impact of house screening and LLIN use on malaria parasite prevalence in children (6 months–13 years) in the intervention compared to the control cohort of the study.

#### Entomological outcomes

##### Primary objective

To evaluate the impact of house screening and LLINs on mosquito host-seeking and indoor resting densities.

##### Secondary objective

To evaluate the impact of house screening and LLINs on the entomological inoculation rate.

#### Socio-economic outcomes

##### Primary objective

To assess the incremental costs of house screening as a supplementary mosquito abatement tool.

##### Secondary objectives

To explore the acceptability of house screening as a malaria control tool in the community.

#### Trial design {8}

This study is a multicounty, two-armed household randomized controlled trial using a generalized randomized block design, with the village as the block. Prior to the selection of the study households in each of the three study locations in the three countries, a baseline household census will be conducted in each village in the target areas. A database of study households that meet the eligibility criteria will then be generated.

During the household census, household access to LLINs will be assessed to ensure that there is an LLIN for every sleeping place in the enumerated household, assuming two people use a single net. House type and potential mosquito entry points for each enumerated household will also be recorded. If the household does not have an LLIN for every sleeping space, this will be issued during the baseline household socio-demographic survey that will be conducted after the household census. The socio-demographic survey will be conducted in 800 randomly selected study households. After the baseline socio-demographic survey, one child between 6 months and 13 years will be randomly selected from the 800 study households to be included in the study cohort. This study cohort will then be screened for malaria parasites (parasitological survey) at the beginning and end of the transmission season. Sentinel households, 120, will be selected from the enrolled study households for an entomological sampling of adult mosquitoes. Exposure to indoor mosquito bites will be estimated by routine surveillance of the sentinel households using CDC light traps and while indoor mosquito resting densities will be estimated using Pyrethrum Spray Catch (PSC) technique. Three months prior to the start of the transmission season (January-May), 400 enrolled households will be randomized to the intervention arm and all mosquito entry points (windows, eaves and doors) screened.

The remaining 400 households will be assigned to the control (no-screening) arm. Households lost to follow-up will be replaced with non-randomized households enumerated during the household census.

As malaria risk may vary between villages, the number of intervention and control households per village will be balanced. A maximum of 10% of all households per village will be enrolled for house screening to avoid the potential diversion of mosquitoes from screened to non-screened households. A similar number of households will be assigned to the control arm in the same village so that the number of intervention and control households will be evenly distributed in each village across the study sites.

The main study outcome will be clinical malaria incidence monitored in the study children cohort by actively following each child enrolled in the study (active case detection-ACD), measuring their body temperature every fortnight for a period of 3–6 months during the high malaria transmission season (January to May) for 2 subsequent transmission seasons of the study. Children presenting with a fever above 37°C or reporting febrile illness in the past week will be tested for malaria using an RDT. The secondary outcome will be parasite prevalence assessed by screening study children at the beginning and end of each transmission season for the 2 consecutive transmission seasons of the study. Vector biting and resting densities indoors will be monitored throughout the study period using CDC light traps and PSC techniques in intervention and control sentinel houses. Acceptability of the proposed intervention, cost of house screening vis a vis LLINs, and the feasibility of scale-up to the community will be assessed using focus group discussions (FGDs) and key informant interviews (KII) with project stakeholders (Fig. 1).

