##### *Entomological endpoints*

The primary entomological endpoint will be the relative indoor mosquito density, expressed as the average number of mosquitoes caught per trap night in each study arm. The secondary endpoint will be the entomological inoculation rate (EIR) incorporating the blood meal source (human biting rate) and the mosquito sporozoite positivity per study arm.

A total of 30 sentinel houses per study arm (*N*=60) per country will be randomly selected for adult mosquito collections. The household selection will be stratified by village and geographical area so that an equal number of sentinel houses are selected in each village and equally spread over the study area. This stratified randomization by the village will reduce the likelihood of imbalances between study arms. Indoor host-seeking mosquitoes will be collected for 5 days each month using CDC UV light traps from 15 sentinel households. The CDC light trap will be placed next to the sleeping space of the study enrolled child and will be raised 1.5 m from the ground. The light trap will be set up at 7:00 p.m. and mosquitoes collected at 7:00 a.m. the next morning.

Indoor resting mosquitoes will be collected using pyrethrum spray catches (PSC) in the remaining 15 sentinel households in each arm of the study. The collections will be done inside the room where the child recruited into the study cohort sleeps. Mosquito sampling using PSC will be conducted early in the morning between 06:00 and 08:00 h. All the exit points to the sleeping area will be shut and a white sheet spread on the floor. An insecticide will then be sprayed in the room to knock down mosquitoes which will then be collected after 10 min. This sampling will be conducted 1 day for each month in the fixed sentinel households throughout the study period.

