##### *Entomological*

House screening is projected to reduce indoor malaria vector collections by at least 50% [51]. We used the *Hayes and* Bennet model for sample size calculation when using means to determine the number of households required to demonstrate a 50% reduction of indoor-entering mosquitoes associated with house screening, with 80% power at the 5% level of significance [50]. A study assessing different mosquito sampling schemes using light traps and human biting catches in Nyimba district, Zambia, in 2014, estimated that 2.6 *An. funestus* were caught using CDC light traps per night [52]. Using Eq. 2 below, we estimated that we would require 17 houses in each arm of the study. An additional 12 households were recruited for mosquito sampling to make a total of 30 households per study arm to allow for sampling of mosquitoes using both the CDC LTs and PSC techniques. Each sampling technique was used to sample mosquitoes from 15 households per study arm. As the standard deviation (SD) for this data was not reported, we assumed a SD of 1.96 for the sample size calculation.

Mosquito data from Chokwe in Mozambique was not available, and there we used the same sample size as that of Zambia of 30 households per treatment arm.
2$$ \mathrm{n}={\left({\mathrm{z}}_{\upalpha /2}+{\mathrm{z}}_{\upbeta}\right)}^2\left({\sigma_0}^2+{\sigma_1}^2\right)/{\left({\upmu}_0\hbox{-} {\upmu}_1\right)}^2 $$

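### The 120 sentinel households fit neither 60 per country nor a three-country total, and the 15 light-trap houses per arm fall below the protocol's own requirement of 17

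*Protocol article*

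**What the plan says.** - **Trial design {8}:** "Sentinel households, 120, will be selected from the enrolled study households for an entomological sampling of adult mosquitoes". The text does not say whether this is per country, for some countries, or for the whole trial. The neighbouring counts are 800 surveyed households and 400 in each arm. The Abstract shows that these are per area: "Eight hundred households will be enrolled in each study area".
- **Outcomes {12}, Entomological endpoints:** "A total of 30 sentinel houses per study arm (*N*=60) per country will be randomly selected for adult mosquito collections". For light traps: "Indoor host-seeking mosquitoes will be collected for 5 days each month using CDC UV light traps from 15 sentinel households". For spray catches: "in the remaining 15 sentinel households in each arm of the study", which shows that the 15 light-trap houses are also per arm. The primary entomological endpoint is the mean catch per trap night in each arm.
- **Sample size {14}, Entomological:** 17 houses per arm are said to give 80% power at the 5% level for a 50% reduction from 2.6 mosquitoes per light-trap night, with an assumed SD of 1.96. Then: "An additional 12 households were recruited for mosquito sampling to make a total of 30 households per study arm". And: "Each sampling technique was used to sample mosquitoes from 15 households per study arm". Mozambique takes the same 30 per arm as Zambia. Zimbabwe is not mentioned there.

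**The concern.** The number of sentinel houses is the sample size for the entomological comparison, and the protocol gives two figures for it without reconciling them. Read on the same footing as the counts beside it, 120 is twice the 60 per country given later.

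The sample-size text raises a second problem. It derives a requirement for light-trap catches, then divides the houses between two collection methods, so that fewer houses than required supply the light-trap endpoint. A reader who takes 30 per arm as comfortably above 17 would think the primary entomological comparison has at least its planned 80% power. The clinical primary endpoint is not affected.

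**Working it through.** **1. The counts side by side**

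- Outcomes: 30 per arm × 2 arms = 60 per country; 30 ÷ 2 methods = 15 per method per arm. The sample-size section agrees on 30 and 15.
- 120 read per country: contradicts 60.
- 120 read as the three-country total: 3 × 60 = 180, so it does not match.
- 120 read as a two-country total: 2 × 60 = 120. This matches, but Trial design speaks of three locations in three countries and limits nothing to two.

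**2. The sum in the sample-size section**

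17 + 12 = 29, not 30. A total of 30 needs 13 additional houses.

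**3. Reproducing the 17**

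Inputs from the sample-size section: means 2.6 and 1.3 (difference 1.3); SD 1.96; 80% power; two-sided 5%, since Eq. 2 uses z for α/2. Only one SD is given, so using it in both arms is an assumption.

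Eq. 2: n = (1.960 + 0.842)² × (σ₀² + σ₁²) / (μ₀ − μ₁)², where (1.960 + 0.842)² = 7.849 and 1.3² = 1.69.

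- SD 1.96 in both arms: 7.849 × (3.842 + 3.842) / 1.69 = 35.7, so 36 houses per arm. The stated 17 is not reproduced.
- One variance term only: 7.849 × 3.842 / 1.69 = 17.8, so 18.
- Poisson variances: 7.849 × (2.6 + 1.3) / 1.69 = 18.1, so 19.
- Working back from 17: σ₀² + σ₁² = 17 × 1.69 / 7.849 = 3.660, a common SD of √(3.660 / 2) = 1.35.

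The second and third variants come close to 17, but neither is Eq. 2 with the stated SD in both arms. The protocol does not show which inputs were used.

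**4. Power at the 15 houses per arm that carry light traps**

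Power = Φ(1.3 / √((σ₀² + σ₁²) / 15) − 1.96), with one observation per house.

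| Variance assumption | σ₀² + σ₁² | Houses per arm for 80% | Power at 15 |
|---|---|---|---|
| SD 1.96 in both arms | 7.683 | 36 | 44% |
| Variance proportional to mean | 5.762 | 27 | 55% |
| SD halved in screened arm | 4.802 | 23 | 63% |
| Poisson | 3.900 | 19 | 72% |
| One variance term | 3.842 | 18 | 73% |
| Implied by the stated 17 | 3.660 | 17 | 75% |

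For example, SD 1.96 in both arms gives 1.3 / √(7.683 / 15) = 1.816, and Φ(1.816 − 1.96) = 0.443. None of these assumptions brings 15 houses to 80%.

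**The case against.** The operational sections are explicit and agree with each other: 60 per country, 30 per arm, 15 per method per arm. Against them, the 120 is one unscoped figure in a summary. It may be an older total for Zambia and Mozambique, the only countries in the sample-size section and the only ones that Trial status reports as fully recruited. This stands as a possible origin. It does not make the text right, because the figure would still lack its scope and leave out Zimbabwe.

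A reader might infer that the design is either 30 or 15 houses per method per arm, and that power differs by about 29 points between the two. The documents do not support this. No section states 30 per method per arm; that figure comes only from assuming 120 is per country and halving it twice. The 29 points (72.9% against 44.3%) also need an SD of 1.96 in both arms, which does not reproduce the 17. On the variance implied by 17 the gap is about 21 points (96.1% against 74.9%).

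It may be said that 30 houses per arm exceed 17. They do, but the 17 was derived from light-trap catches and the endpoint is per trap night. The spray-catch houses contribute no trap nights.

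The formula also uses one count per house, whereas light traps run 5 days a month and a mixed model is planned. This stands: the powers above are indicative and are not forecasts of the power of the final analysis. The shortfall of 15 against 17 does not depend on them.

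**Conclusion.** The point holds as a sample-size figure that is wrong or lacks its scope, together with a planned power that the stated allocation does not deliver on the protocol's own method. Three statements need no variance assumption: 120 fits neither 60 per country nor 180 in total; 17 + 12 is 29; and 15 light-trap houses per arm are fewer than the required 17.

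The size of the power shortfall depends on the variance. Power is about 75% if the variance implied by 17 is right, and about 44% if the SD is 1.96 in both arms, in which case the requirement itself should be 36. Both figures assume one independent observation per house.

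It would go too far to say that only a reading of 120 per area comes near 80%. On the variance implied by 17, 15 houses already give about 75%. The low figure of 44% comes from the mismatch between the SD of 1.96 and the 17, not from the 120. Nor do the documents show that country teams worked to different numbers.

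**What to change.** 1. State one sentinel figure, with its scope, in every section. If the Outcomes and Sample size sections hold, Trial design should read 60 per country (30 per arm, 15 per trapping method per arm), 180 in total. If some other number was intended, all three sections should be brought into line with it.
2. Correct the addition of 17 and 12.
3. Recheck the 17 against Eq. 2, and state the SD used in each arm and whether it refers to nights or to houses.
4. Restate the power for the 15 houses per method per arm actually used. If repeated trap nights are counted on, say so and give the assumed variation between and within houses.

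The cost is a wording correction and a recalculated power figure, which may be less favourable. No new houses are needed.

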##### Criteria for discontinuing or modifying allocated interventions {11b}

Withdrawals may also occur if a study subject has any significant adverse events such increase in upper respiratory tract infections (URTis) in household members in screened households compared to non-screened households.

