#### Participant timeline {13}

#### Sample size {14}

##### *Clinical*

The sample size used in this study is based on simulation models described in *Hayes and Bennet* et al. for incidence rates [50]. Routine data collected from all health facilities in Nyimba district in Zambia estimated an incidence rate of 0.312 cases per person from January to June 2019. Using these estimates in Eq. 1 [50], we estimated that in order to detect a reduction of 35% on malaria incidence, with 80% power at the 5% significance level, 338 houses were required per study arm when following one child per household per year [51]. A total of 400 households with one child each were recruited per treatment arm. The additional households were enrolled to account for households lost to follow-up.

Data collected from all health facilities in Chokwe district, Mozambique, estimated an incidence rate of 0.325 cases per person from January to June. Using the same formula, we estimated that 324 children were required per treatment arm to observe a 35% treatment effect with 80% power at the 5% significance level [50]. A total of 400 households were also recruited in Mozambique.
1$$ \mathrm{y}={\left({\mathrm{z}}_{\upalpha /2}+{\mathrm{z}}_{\upbeta}\right)}^2\left({\uplambda}_0+{\uplambda}_1\right)/{\left({\uplambda}_0\hbox{-} {\uplambda}_1\right)}^2 $$

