##### *Recruitment {15}*

Study participants will be recruited by the national project team in consultation with local health workers. The project staff will obtain verbal and written informed consent using ethical review committee (ERC)-approved language that outlines the objectives, benefits, and potential risks of the study and the data and biological samples that will be collected. Household heads will be briefed about the study, provided with an information sheet, and asked for their written consent to have their children involved in the study. Assent will be sought from all children above the age of 10 years. Household heads/guardians who do not want their children to participate in the study will be free to refuse participation. On the survey day, children will be informed about the survey procedures, making it clear that their participation is voluntary and that they might opt-out at any time if they chose to. Children unwilling to participate or whose parents did not give consent will be excluded from the selection procedure, with assent obtained from selected children before samples are collected. Participants’ names will be removed from the final database to ensure anonymity. Children with a positive malaria RDT will be treated for malaria according to national guidelines.

Participants will be free to withdraw from the study at any time without giving a reason. In the unlikely event that homeowners require their house to be returned to the pre-intervention state, items added will be removed. No replacements will be made during the surveillance period in either year, but in year 2, children who have withdrawn or are no longer in the study for any reason will be replaced by a child within the age range of 6 months—13 years in the same household. If another child within this age range is not present in that house, then another household with a child within this age range will be sampled in the same village. If a household withdraws consent, no further follow-up will be made in that household. All data collected up until the point of withdrawal will be kept for the per-protocol analysis at the end of the study. If the house was participating in the entomology collections, it will be replaced by a neighboring house of the same type and intervention status.

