#### Methods in analysis to handle protocol non-adherence and any statistical methods to handle missing data {20c}

A per-protocol and an intention-to-treat analysis will be conducted.

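### Replacing lost households with non-randomized ones, and tying pre-withdrawal data to the per-protocol analysis, leaves the randomized comparison unprotected

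*Protocol article*

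**What the plan says.** The household is the unit of randomization, stratified by village (Sequence generation {16a}). Four parts of the Protocol article govern what happens when one is lost.

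- **Trial design {8}:** "Households lost to follow-up will be replaced with non-randomized households enumerated during the household census". No timing is given.
- **Recruitment {15}, replacement:** "No replacements will be made during the surveillance period in either year, but in year 2, children who have withdrawn" or otherwise left are replaced, first by another eligible child in the same household. If there is none, "then another household with a child within this age range will be sampled in the same village". A house lost from the entomology collections is handled separately: "it will be replaced by a neighboring house of the same type and intervention status".
- **Recruitment {15}, withdrawn households:** follow-up stops once a household withdraws consent, and "All data collected up until the point of withdrawal will be kept for the per-protocol analysis at the end of the study".
- **Section {20c}:** "A per-protocol and an intention-to-treat analysis will be conducted". Neither set is defined, and neither is named as primary.

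On enrolling 400 per arm against 338 required in Zambia, Sample size {14} says: "The additional households were enrolled to account for households lost to follow-up". Mozambique also enrols 400, against 324 required.

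**The concern.** Randomization makes the two arms comparable only for the households that were randomized. All 800 enrolled households per country are allocated, so a different household brought in later must come from outside that set, as Trial design {8} says outright. Nothing states how it is drawn or how it receives an arm. Screening is visible to field staff and researchers (Who will be blinded {17a}), so whoever selects a replacement can know which arm is being filled.

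Losses may also differ by arm. Section {11b} says "Withdrawals may also occur if a study subject has any significant adverse events such increase in upper respiratory tract infections", and frames this as screened against non-screened households. Recruitment {15} lets owners have added items removed, a request that arises only in screened houses. If the households lost, and those that replace them, differ in malaria risk by arm, the rate ratio is biased, and a larger sample does not cure that.

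The rule on withdrawn households points the wrong way. Intention-to-treat is the analysis that most needs the child-time before withdrawal, and it is the one not mentioned there.

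**Working it through.** **1. The plan's sample sizes (Sample size {14}, Eq. 1).** Inputs: control rate λ0 = 0.312 (Zambia) and 0.325 (Mozambique), 35% reduction, two-sided 5%, 80% power, so (1.96 + 0.8416)² = 7.849.

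n = 7.849 × (λ0 + λ1)/(λ0 − λ1)², with λ1 = 0.65 λ0.

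- Zambia: 7.849 × 0.5148/0.1092² = 338.8 (stated 338).
- Mozambique: 7.849 × 0.53625/0.11375² = 325.3 (stated 324).

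Both reproduce to within about one household. The section gives no calculation for Zimbabwe.

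**2. Loss that 400 per arm absorbs without replacement.**

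- Zambia: 1 − 338/400 = 15.5% (62 households).
- Mozambique: 1 − 324/400 = 19.0% (76 households).

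**3. Power without replacement.** Power = Φ[(λ0 − λ1)/√((λ0 + λ1)/n) − 1.96], with n = 400 × (1 − loss). The loss rates are assumptions, because the documents give none.

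| Loss | n per arm | Zambia | Mozambique |
|---|---|---|---|
| 0% | 400 | 86.1% | 87.4% |
| 10% | 360 | 82.3% | 83.8% |
| 15.5% | 338 | 79.9% | 81.5% |
| 20% | 320 | 77.7% | 79.4% |

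These figures count a lost household as contributing nothing. Under the fix below it contributes its child-time up to loss, so in that respect they are pessimistic.

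**4. Size of a possible bias (illustration only).** Suppose a fraction f of the intervention arm's child-time comes from replacement households with r times the risk of those they replace, the lost households had average risk, and the control arm has no replacements. The rate ratio is multiplied by 1 − f + f × r. Take a true ratio of 0.65, f = 15.5% (the full Zambian allowance) and r = 0.7 or 1.3.

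- Replacements cover all follow-up, f = 0.155: factors 0.9535 and 1.0465, a shift of about 4.7%. Then 0.65 × 0.9535 = 0.62 and 0.65 × 1.0465 = 0.68.
- Replacements enter in year 2 only, with two equal seasons pooled, f = 0.155/2 = 0.0775: factors 0.97675 and 1.02325, a shift of about 2.3%. Then 0.65 × 0.97675 = 0.635 and 0.65 × 1.02325 = 0.665.

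The second case follows the timing in Recruitment {15}. Same-household replacement, or similar replacement in the other arm, would shrink either figure.

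**The case against.** There are several fair points on the plan's side.

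- **An intention-to-treat analysis is planned.** Section {20c} commits to one, and it can still be done properly if replacements are excluded and pre-withdrawal data included. Detailed analysis sets are commonly left to an analysis plan that is not shown. This stands against any claim that the trial has already lost its randomized comparison. It does not remove the defect, because the replacement rule and the data rule are written down and point the other way.
- **Recruitment {15} limits the damage.** It bars replacement during surveillance and tries the same household first, which keeps the randomized unit. This stands and reduces the affected fraction.
- **No selection mechanism is stated.** A reader might infer that replacements are hand-picked with the arm in mind. The text says only that a household is sampled in the village. Arbitrary selection is an open risk and not a described procedure.
- **Sentinel houses.** Only trial houses are screened, so a screened replacement would most naturally already be a randomized house, and the entomological endpoint is the one affected. This weakens the point for the screened arm. The text still chooses the house by its known status and does not require it to be randomized.
- **The bias figures are assumed.** They are. They put the whole allowance in one arm and take the 30% difference as given.

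**Conclusion.** The point stands as a stated rule that needs correcting before analysis. Followed literally, non-randomized households can enter the arm comparison, and some randomized child-time may be left out of the analysis that most needs it. On the assumptions above, the rate ratio moves by about 2.3% if replacements enter in year 2 only and about 4.7% if they cover all follow-up. That is modest, but it can go in either direction and is avoidable. Replacement gains little, since the enrolment margin already covers 15.5% loss (Zambia) or 19% (Mozambique) at close to 80% power.

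Three stronger readings are tempting but not supported.

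- Pre-withdrawal data are not said to be reserved exclusively for the per-protocol set. The text is silent on intention-to-treat.
- Trial design {8} and Recruitment {15} do not contradict each other on timing. The first gives none and the second supplies it.
- Follow-up is not said to end when screens are removed or the intervention stops. It ends when the household withdraws consent.

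**What to change.** Reconcile Trial design {8}, Recruitment {15} and section {20c}:

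1. Name intention-to-treat as the primary analysis: all originally randomized households in their assigned arm, with all child-time up to loss or withdrawal.
2. Flag replacement households and replacement sentinel houses in the database and use them only in a sensitivity analysis. A replacement child in the same randomized household may stay in the primary analysis.
3. Amend Recruitment {15} so that data up to withdrawal are kept for both the intention-to-treat and the per-protocol analyses.
4. State how any replacement household is drawn and given its arm.

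The cost is a few sentences and one data flag. The downside is somewhat fewer child-months in the primary analysis. By Eq. 1, power drops below 80% in Zambia once loss exceeds about 15.5%, and at 20% loss it is 77.7% there and 79.4% in Mozambique.
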